#### Explicit, exogenous stress-regulation – emotional stroop task

We expect that MBSR will affect participants’ responses when they are asked to identify and respond to emotionally conflicting information. In terms of behaviour, we expect to observe this as a reduction in response time in incongruent emotional situations. On our brain imaging measurements, we expect that MBSR will enhance ECN and SN within-network connectivity during emotional conflict processing. We will statistically test differences in behavioural outcome measures (reaction time and accuracy) between groups with linear mixed-effect regression analysis. Fixed factors will include group (MBSR, wait-list), time (baseline, post-treatment), congruency (congruent, incongruent), as well as a group x congruency x time interaction. Additional fixed factors will be added (university, sex, age, and recruitment wave) and a random intercept for participants will be included to account for individual differences.

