#### Explicit, exogenous stress-regulation – emotional conflict resolution task

We will explore explicit, exogenous regulation by assessing behavioural responses and brain activity during a Stroop-like emotional conflict resolution task as described by Etkin et al. (2006). This task requires explicit attentional control and response inhibition over emotional processing that arises from conflicting external emotional information. The task consists of 148 presentations of happy or fearful facial expression photographs chosen from the set of Ekman and Friesen (1976). Faces are cropped and the words ‘‘FEARFUL’’ or ‘‘HAPPY’’ are written across the face in Dutch (i.e. “BANG”, “BLIJ”), such that word and expression are either congruent or incongruent. Stimuli are presented for 1 s, with a varying interstimulus interval of 3–5 s, during which a central fixation cross is shown. Participants are instructed to respond as fast and accurately as possible, by selecting the response buttons corresponding to ‘‘fearful’’ or ‘‘happy’’ for the expression on the face. This task is designed to probe emotional conflicts by manipulating the congruency of the stimuli. Congruency refers to whether the two types of stimuli shown simultaneously in this experiment (i.e., facial expression and written word) match or not. For example, when a facial expression matches the word superimposed on it is considered a congruent trial, and when the facial expression does not match the word superimposed on it is considered an incongruent trial.

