### Statistical analysis

#### Sample size calculation

The sample size, which is reported on http://trialregister.gov, was calculated on the basis of our planned Analysis of Covariance (ANCOVA) to estimate the difference between groups in perceived stress at post-treatment, while taking into account individual baseline measurements of perceived stress as a covariate. We use the method of Borm, Fransen, & Lemmens (2007), which adjusts the sample size calculated for an independent sample t-test by multiplying with the factor (1-r^2), where r is the correlation coefficient between baseline and post-treatment measurement. We aim to achieve a power of 80% with an *α* = 0.05. The correlation between baseline and end-of-treatment perceived stress is estimated at *r* = 0.7, based on data from Verweij et al. (2018). Assuming a moderate effect size of Cohen's *d* = 0.4, as reported by a large RCT on a general student sample (Galante et al., 2018), we would need 54 participants per group. Taking also into account an average attrition rate (10%) of studies on student populations reported in a meta-analysis by Khoury et al. (2015), we aim to recruit a total of 60 participants per group.

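### Stroop accuracy, a right/wrong outcome, is assigned a linear mixed model, so a general accuracy gain can appear as a congruency-specific effect

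*Protocol article*

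**What the plan says.** The task description (Stress-regulation tasks, emotional conflict resolution task) has participants answer "by selecting the response buttons corresponding to ‘‘fearful’’ or ‘‘happy’’ for the expression on the face". Each response is therefore correct or incorrect. On length, "The task consists of 148 presentations of happy or fearful facial expression photographs"; the split between congruent and incongruent trials is not given.

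The analysis text (Statistical analysis, emotional stroop task) puts both behavioural outcomes under one model class: "We will statistically test differences in behavioural outcome measures (reaction time and accuracy) between groups with linear mixed-effect regression analysis". The terms are: "Fixed factors will include group (MBSR, wait-list), time (baseline, post-treatment), congruency (congruent, incongruent), as well as a group x congruency x time interaction". It adds university, sex, age and recruitment wave, and "a random intercept for participants will be included to account for individual differences".

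The only behavioural hypothesis for the task concerns speed: "In terms of behaviour, we expect to observe this as a reduction in response time in incongruent emotional situations". The article gives no link function, transformation or separate model for accuracy. It does not say whether accuracy enters per trial or as a proportion per participant and condition. It gives no expected accuracy level.

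**The concern.** The term of interest is an interaction, and whether an interaction exists depends on the measurement scale. For reaction time the linear scale is a reasonable default. For a right/wrong outcome it is not neutral: the same shift in log-odds is worth more percentage points where accuracy is lower. If incongruent trials are harder, as a conflict task intends, a general improvement in attention or effort can produce a larger percentage-point gain on incongruent trials. The linear model then shows a three-way interaction that looks like better handling of emotional conflict.

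A general gain is plausible on the article's own account. The Background reports limited evidence that mindfulness-based interventions affect attention-related functions, the control is a wait-list, and post-treatment assessment is not blinded.

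The linear model also assumes one residual variance, whereas the variance of a right/wrong response is p(1-p) and differs between conditions whenever accuracy does.

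At stake is the reading of accuracy as evidence for the explicit-exogenous domain, one of the four stress-regulation domains.

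**Working it through.** The article states no accuracy level, effect or power for this outcome, so there is no figure of its own to reproduce.

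**Inputs.** From the article: 148 trials per session, 54 analysed per group ("we would need 54 participants per group"), and alpha 0.05, stated there for the primary outcome and taken as two-sided. Assumed: 74 trials per condition, the accuracy levels, the between-person SD on the logit scale (0.6 or 0.7) and the size of the gain.

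**Step 1: a uniform log-odds gain in percentage points.** With starting accuracy p and odds ratio OR, the new accuracy is p' = OR·p / (1 - p + OR·p). The three-way term is (p' - p) on incongruent trials minus (p' - p) on congruent trials. At 97% congruent, 92% incongruent and OR 1.65:
- congruent: odds 0.97/0.03 = 32.33; × 1.65 = 53.35; p' = 98.16%; gain 1.16 points
- incongruent: odds 0.92/0.08 = 11.5; × 1.65 = 18.98; p' = 94.99%; gain 2.99 points
- three-way term: 2.99 - 1.16 = 1.83 points, although the log-odds effect is identical on both trial types.

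At the same OR the term is 1.14 points at 99/96%, 1.78 at 95/90%, 3.15 at 90/80% and 0 at 97/97%. What drives it is the difference between conditions. A ceiling is not needed.

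**Step 2: variance.** p(1-p) is 0.97 × 0.03 = 0.029 for congruent and 0.92 × 0.08 = 0.074 for incongruent trials, about 2.5 times as large.

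**Step 3: how often the three-way term is significant when the true log-odds interaction is zero** (54 per arm, SD 0.6; 2000 linear runs, 60-200 logistic runs per row):

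| Congruent/incongruent | OR | Linear, proportions | Linear, trial level | Logistic |
|---|---|---|---|---|
| 97/92% | 1.00 | 2% | 5% | 3% |
| 97/92% | 1.22 | 8% | 13% | 3% |
| 97/92% | 1.35 | 15% | 24% | 5% |
| 97/92% | 1.65 | 34% | 48% | 4% |
| 90/80% | 1.65 | 37% | 49% | 6% |
| 95/93% | 1.65 | 10% | 12% | 5% |
| 97/97% | 1.65 | 5% | 6% | 3% |

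A second set used SD 0.7, accuracy pairs 97/90, 96/90, 95/85 and 92/85%, and a comparison of arms on the within-person difference of differences. At OR 1.5 the linear rates in one implementation were 48%, 35%, 53% and 24%. Over OR 1.32-1.5 the range across repeats was about 16-57%, with the log-odds test at about 4-6%.

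**Step 4: the reverse case, a gain of 1.5 points on both trial types.** At 97/90%:
- congruent OR: (0.985/0.015)/(0.97/0.03) = 65.67/32.33 = 2.03
- incongruent OR: (0.915/0.085)/(0.90/0.10) = 10.76/9 = 1.20
- ratio: 1.20/2.03 = 0.59, a log-odds interaction in the opposite direction.

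At 92/85% the ORs are 1.25 and 1.13, ratio 0.90. In simulation the linear test stayed at about 5%, while the log-odds test was significant in 10-63% of runs in one implementation and 12-49% in another, depending on the accuracy pair.

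**The case against.** The strongest objection is that the error is defined by the choice of scale. A gain is called general here because it is uniform in log-odds, and nothing in the article says that this is what a general gain means. Step 4 shows that a gain uniform in percentage points makes the logistic test err instead. This stands. A binomial model suits right/wrong data better, but no single scale separates a general from a conflict-specific gain, and the fix has to allow for that.

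The assumed effects are also large. With a logit SD of 0.7, OR 1.5 is ln(1.5)/0.7 = 0.58 SD. The d = 0.4 used for the primary outcome corresponds to exp(0.4 × 0.7) = 1.32, where the linear rates are 16-31%. This tempers the size and leaves the mechanism intact.

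An article may leave to the full plan whether accuracy is aggregated or transformed. That is fair, and the rates are lower on proportions. But the article does name the model class for accuracy, so this is a stated choice and not an omission.

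A reader might go further and infer that accuracy is near its ceiling, that a general gain would necessarily be published as improved conflict regulation, or that accuracy is the behavioural test of this domain. The article supports none of these. It gives no accuracy levels and no rule for interpreting an accuracy interaction, and its behavioural hypothesis is about response time. In most of the scenarios at OR 1.5 or below, the spurious result occurs in fewer than half of the runs.

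**Conclusion.** The concern holds in a limited form. The article assigns a linear mixed model to a binary or bounded outcome, and the three-way term it tests is scale-dependent. If accuracy is lower on incongruent trials and MBSR brings a gain uniform in log-odds, the linear test shows an interaction in about 16-57% of simulated trials at odds ratios of 1.32-1.5, against about 5% with a logistic model. With SD 0.6 and 97/92% accuracy, the rates are 8-24% at odds ratios of 1.22-1.35.

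These figures rest on assumed accuracy levels, trial split and between-person SD. With no accuracy effect, or with equal accuracy in both conditions, the linear test stays at about 2-6%. Accuracy is a secondary behavioural measure of one mechanistic task. The reaction-time model and the primary perceived-stress ANCOVA are not touched. It is a small correction, but worth making before the data are analysed.

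**What to change.** Replace the shared model statement with two sentences:
- Reaction time: linear mixed model, as written.
- Accuracy: trial-by-trial logistic (binomial) mixed model with the same fixed terms and a random participant intercept, with the three-way term read on the log-odds scale.

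Because that term depends on scale, also report the model-based accuracy differences in percentage points by group, congruency and time. State in advance that a conflict-specific accuracy effect will be claimed only if it is seen, in the same direction, on both scales.

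Data collection does not change. The cost is results given as odds ratios plus one extra table, a slightly longer model fit, and a stricter condition for claiming a conflict-specific accuracy effect.

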#### Implicit, endogenous stress-regulation—resting state

Recent literature suggests that mindfulness enhances within-network connectivity of SN, decreases within-network cohesion of DMN, and decreases connectivity between SN and DMN [28]. Furthermore, we expect that MBSR will additionally enhance within-network connectivity of both SN and ECN in the aftermath of exposure to an acute stressor, as well as enhancing connectivity between SN and ECN. To replicate mindfulness connectivity findings and test our hypothesis related to the effects of acute stress statistically, we will perform a network connectivity analysis as described earlier (MRI analysis) with an additional fixed factor determining pre-/post- stress induction data.

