#### Implicit, endogenous stress-regulation – resting under stress

We will assess resting-state functional connectivity within and between large-scale brain networks (ECN, SN, DMN) before and after a stress induction task, in order to investigate implicit, endogenous stress regulation. This task is chosen since it involves measuring spontaneous brain activity that is driven by an internal stressful state following a stress induction. Participants first undergo a resting state fMRI scan, for which they are instructed to keep their eyes open and fixated on a fixation cross on the screen. They are instructed to let their mind wander, without thinking of anything specific, or performing any repetitive mental activities. Shortly after this scan, a stress induction procedure takes place. The procedure is a modified version of the socially evaluated cold pressor test (SECPT), during which a researcher unknown to the participant will enter the MRI lab to perform the stress induction tasks. The researcher asks the participant to immerse their foot in a box of cold water (1.8–2.2 ^o^ C) and try to keep it in for 3 min. The researcher then tells the participant that they are evaluating their facial expressions during the task. The researcher is instructed to abstain from giving positive feedback at all times and to try to keep a neutral facial expression. Once the Cold Pressor Test is over, the participants foot is covered with a towel and the researcher continues with the second part of the stress induction. In this part the participant has to count backwards, in steps of 17 or 13 from the number 1872, or 2013 respectively. The researcher asks them to be as fast and as accurate as possible. If they are too slow the researcher asks them to speed up. If they are incorrect the researcher asks them to start from the beginning. This task also lasts 3 min. After stress induction, a second resting-state fMRI scan is acquired, with the same instructions as before.

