#### Baseline measurements

After inclusion, the participant’s baseline measurements are acquired. First, two visits (on consecutive days) at the Donders Centre for Cognitive Neuroimaging (DCCN) are scheduled. On the first visit participants are asked to perform some of the neurocognitive assessments (Fear Conditioning task, Emotional Conflict Resolution task, and Resting State fMRI task). On the second visit participants are asked to perform a short task, part of the Fear Conditioning task. In addition, they undergo clinical assessments in the form of questionnaires on both days. Participants will then follow a week of ecological momentary assessments, during which they are asked to answer multiple short questionnaires during their daily life. After these baseline measurements, participants are randomly assigned to two groups as described earlier.

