#### Post-intervention

As soon as the MBSR training has concluded, all participants are asked to visit the DCCN for their post-treatment measurements. These visits (visit 3 & 4) are scheduled on consecutive days and will involve the same neurocognitive and clinical assessments as the baseline measurements, with the addition of the Real-time fMRI Neurofeedback task. In addition, another ecological momentary assessment week is planned.

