#### MRI analysis

Neuroimaging data from all tasks will be analysed using various neuroimaging software packages, including FSL, SPM, (Turbo-) Brainvoyager, Nipype, as well as custom analysis scripts. The data will be first pre-processed, to remove artefacts, such as movement and physiological noise. General Linear Models will then be used per participant, per task, with regressors representing task activity, as well as nuisance parameters such as motion parameters and physiological noise parameters. Parameter estimates will then be introduced into second level a mixed-effect model with group (MBSR, wait-list), and time (baseline, post-treatment) as fixed factors, as well as a group x time interaction. Additional fixed factors will be added (university, sex, age, and recruitment wave). A random intercept for participants will be included to account for individual differences. In all tasks we will assess brain connectivity patterns of three large-scale brain networks (SN, ECN, DMN). Connectivity will be operationalised as the correlation coefficients between activity time-courses of nodes of these networks. Within- and between-network connectivity will be calculated to determine network cohesion and between-network communication, respectively. Potential connectivity patterns we observe (e.g., changes in SN or ECN within-network connectivity) will be tested as potential moderators of the clinical outcome post-treatment.

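### Resting-state model: four scans per person in two sessions but only a participant intercept, so the group x time error is right only if unstated variances happen to balance

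*Protocol article*

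**What the plan says.** All places are in the protocol article.

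- **Scans per session.** In the section on resting under stress, "Participants first undergo a resting state fMRI scan". The cold pressor and arithmetic stressor follow, and then "After stress induction, a second resting-state fMRI scan is acquired, with the same instructions as before".
- **Sessions.** The first baseline visit covers the "Fear Conditioning task, Emotional Conflict Resolution task, and Resting State fMRI task". The post-treatment visits "will involve the same neurocognitive and clinical assessments as the baseline measurements". The Design section puts them three months after baseline. That makes 2 x 2 = 4 resting scans per participant.
- **General second-level model (MRI analysis).** The fixed part is "group (MBSR, wait-list), and time (baseline, post-treatment) as fixed factors, as well as a group x time interaction", plus university, sex, age and recruitment wave. For the random part, "A random intercept for participants will be included to account for individual differences". No other random term or residual correlation is stated.
- **Resting-state analysis.** This model is reused: "we will perform a network connectivity analysis as described earlier (MRI analysis) with an additional fixed factor determining pre-/post- stress induction data". No random term is added, and no interaction of stress phase with group x time is stated. The fear-conditioning and Stroop sections, by contrast, each name a three-way interaction.

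The one analysis serves two hypotheses. The first is a replication of known mindfulness effects on connectivity. The second is an additional enhancement of connectivity after the acute stressor.

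**The concern.** With one estimate per person and visit, a participant intercept is enough. The difficulty starts when the resting-state section brings a second scan into each session without a term for the session.

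A lone participant intercept makes every pair of a person's scans equally correlated. Two scans from the same session may share that day's state, and people may also differ in how connectivity changes between visits. Either produces participant-by-visit variance, and group x time should be judged against an error that includes it. People may also differ in how they react to the stressor, which produces participant-by-phase variance. The stated model has neither component and uses one pooled within-person error for every test.

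At stake is the nominal error rate of the replication test and the validity of the post-stress test, both of which serve the mechanistic aims.

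**Working it through.** The article states no figure for this analysis, so there is none to reproduce. The check uses variance algebra, supported by simulation.

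**Inputs.** From the article: four scans per person, 54 per group (Sample size calculation), alpha 0.05 (two-sided assumed). Assumed, because the documents give nothing: scan residual variance 1, participant-by-visit variance *pv* from 0.25 to 2, and participant-by-phase variance *ps* at several multiples of *pv*. Complete, balanced data.

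**Step 1: true variances of the three within-person contrasts (unit-length contrasts).**
- visit: 1 + 2pv
- phase: 1 + 2ps
- visit x phase: 1

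**Step 2: what the stated model uses for all three.** The average: M = 1 + (2pv + 2ps)/3.

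**Step 3: ratio R of true to modelled variance.**
- group x time: R = (1 + 2pv)/M
- group x time at the post-stress scan only: R = (2 + 2pv)/(2M) = (1 + pv)/M
- group x time x phase: R = 1/M

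True type I error = 2[1 - Phi(1.96/sqrt(R))].

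Example, group x time, pv = 0.5, ps = 0: R = 2/1.333 = 1.5; 1.96/1.225 = 1.60; type I error 11.0%.

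**Step 4: results at nominal 5%.**

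| pv | group x time, ps = 0 | group x time, ps = pv/2 | group x time, ps = 2pv | post-stress scan only, ps = 0 | three-way, ps = 0 |
|---|---|---|---|---|---|
| 0.25 | 8.4% | 7.4% | 5.0% | 5.8% | 3.4% |
| 0.5 | 11.0% | 9.0% | 5.0% | 6.5% | 2.4% |
| 1 | 14.4% | 11.0% | 5.0% | 7.4% | 1.1% |
| 2 | 18.1% | 12.9% | 5.0% | 8.4% | 0.3% |

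With ps above 2pv the visit test is conservative. At pv = 0.5, ps = 2: R = 2/2.667 = 0.75, type I error 2.4%.

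**Step 5: where each test is right.** Setting R = 1 gives ps = 2pv for group x time and ps = pv/2 for the post-stress-scan test. The three-way test needs both variances to be zero. Under either reading of the second hypothesis, both hypotheses therefore have correct errors together only if pv = ps = 0.

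**Step 6: simulation (20,000 runs, 54 per group, ps = 0).** Group x time under the stated model rejected in 8.4%, 10.9% and 14.2% of null trials for pv = 0.25, 0.5 and 1. Tested against its own between-session error, it rejected in 4.8-5.1% across all scenarios. In a small set of mixed-model fits (60 runs, pv = 0.5), the mean standard error was 0.221 with a participant intercept only and 0.270 with a participant-by-visit term. The true value is sqrt(2 x 2/54) = 0.272.

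**The case against.** The strongest reply is that no variance component for connectivity appears in the documents, so neither the size nor the direction of the error is known. This stands. The stressor is placed between the two scans precisely to change the participant's state, so phase variance is plausible, and enough of it brings group x time back to 5% or below. Motion and physiological noise are also to be regressed out, which may shrink the shared session component. Against this, the Background expects changes in these measures to go along with clinical changes and looks for individual differences in benefit. That suggests visit change varies between people, but gives no size.

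Several stronger readings are tempting and are not supported:

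- **That same-session scans are treated as fully independent.** The participant intercept already correlates all four scans. Only the extra same-session similarity is left out.
- **That group x time is right only if both variances are zero.** It is also right when phase variance is twice visit variance.
- **That the post-stress hypothesis necessarily loses power.** This follows only if it is tested as group x time x phase, which the resting-state section does not state. Tested as group x time at the post-stress scan, it is mildly inflated with zero phase variance and correct when phase variance is half the visit variance.
- **That inflated degrees of freedom drive the problem.** About 318 against 106 changes the critical value only from about 1.98 to 1.97. The wrong variance is what matters.

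It can also be said that a journal article leaves covariance details to the analysis plan. Here, however, the random structure is stated and then explicitly reused for a design with one more level of nesting.

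**Conclusion.** The point holds in conditional form. As stated, the resting-state model imposes equal correlation on scans that are minutes apart and scans that are about three months apart, and it judges all within-person contrasts against one pooled error.

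Over the assumed range of visit variance (0.25 to 2 times the residual), the true type I error of group x time is about 8-18% with no phase variance and about 7-13% with phase variance half the visit variance. It is 5% at twice the visit variance and conservative above that. The post-stress hypothesis is conservative as a three-way interaction. As group x time at the post-stress scan it runs at about 6-8% with zero phase variance.

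These figures rest on assumed variance ratios, complete data and 54 per group. A reader might infer that a positive replication result would be a false one, or that the trial's main result is at risk. Neither follows: the direction of the error is unknown, and the primary PSS ANCOVA is a separate analysis that this does not touch. It is a secondary, mechanistic analysis with a defect that is cheap to remove before the data are analysed.

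**What to change.** In the resting-state analysis section, state the random part of the model separately and do not inherit it from the MRI analysis section: random intercepts for participant, participant-by-visit and participant-by-phase, with Satterthwaite or Kenward-Roger degrees of freedom. A more flexible alternative, not an equivalent one, is an unstructured 4 x 4 within-person covariance over the four scans. Name the contrast that tests the post-stress hypothesis (group x time x phase, or group x time at the post-stress scan), and test it and group x time in that model.

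The cost is a sentence or two and no new data. The random-intercept version adds two variance parameters to the present two. The unstructured version has ten in all. Intervals for group x time may become wider, which is the honest price if session-level variation is present.
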